**Visit 2: Discussion of Screening results (Optional visit)**

Discussion of results: Participants may have their results discussed over the phone or may choose to return to CRC to have their results discussed in person.

Subjects with normal glucose tolerance, IFT or IGT AND plasma vitamin 25(OH) D level of between 20 and 50 nmol/L (inclusive) will proceed with randomisation to either receive Vitamin D or Placebo

- Urine pregnancy test will be performed in women who fulfil criteria to proceed with phase 2 of study- pregnant women will be excluded from phase 2 participation

.

Subjects with normal glucose tolerance and with level of Vitamin D > 50nmol/L will be reassured and excluded from further participation of trial

Subjects with abnormal glucose tolerance (IFT or IGT) and Vitamin D level of > 50nmol/L will be excluded from further participation of trial and will be referred for appropriate follow up.

Subjects with fasting glucose of > 7mmol/L and/or 2 hour glucose >11.1 mmol/L will be referred back to primary health care for repeat assessment to confirm or rule out diagnosis of Diabetes.

Subjects with vitamin D level of <15nmol/L will be referred back to primary health care for appropriate assessment.

Subjects found to have abnormal renal, liver and bone function test will be referred back to primary health care for appropriate assessment.

Eligible subjects will be invited to proceed with study by returning for Visit 3.

**Visit 3: Randomisation:**

Randomization assessment will include:

- Record of urine pregnancy test results
- Record of concomitant medications- ensure patient has not been started on vitamin D in the interim between screening and randomization assessment
- Physical activity are quantified using the validated Paffenbarger Physical Activity Questionnaire^30^
- Blood pressure measurement- average of 3 readings (sitting)

Subjects eligible to proceed with study will be randomised to either receive Vit D3 4000iu per day or placebo.

**Visit 4,5, :Follow up visits:**

All subjects will be seen every 8 weeks (+/-1 week) to be dispensed supply of Vitamin D or placebo. Compliance will be checked with pill count. Any side effects will be monitored.

At Visit 4, blood sample will be taken for calcium, phosphate and albumin

**Visit 6: Assessment at study completion:**

At the end of 6 months- all subjects will attend fasting and have

- Repeat clinical examination- including
  - Blood pressure measurement- average of 3 readings (sitting)
  - BMI
  - Waist: Hip ratio
- Repeat 75g Oral Glucose tolerance test—with measurement for
  - glucose and Insulin at time 0,60,90 and 120 minutes
- Repeat Blood tests for plasma 25(OH) D, calcium, phosphate and albumin, lipid profile, HsCRP and Urinary microalbumin-creatinine ratio.

The study will be conducted in Clinical Research Unit of Hospital Pulau Pinang.

## Schematic diagram of study design:

Design of a randomized, controlled, double-blind clinical trial

Screening Results Randomisation Trial Observation Study ends

Assessment Treatment Period

|  |  |  | Vit D3 4000 iu PO od |  |  |  |  |
| --- | --- | --- | --- | --- | --- | --- | --- |
|  |  |  | Placebo |  |  |  |  |

| Visit No. 1 | 2(optiona) | 3 | 4 | 5 |  | 6 |
| --- | --- | --- | --- | --- | --- | --- |
| Timeline -2wk | -1wk | 0 (+/-1) wk | 8(+/-1)wk | 16(+/-1)wk |  |  |

## Study population

### *Inclusion criteria*

a) Provision of written consent by subject

b) Female patients who fullfill ALL of criteria below

- - Previous Gestational Diabetes-according to WHO criteria or as documented on medical record
  - 6-48 months postpartum from GDM pregnancy
  - Negative Pregnancy test at screening
  - With no plan to conceive again within the 6 months of study duration
  - With 75g OGTT at baseline confirming either normal respond, IFT or IGT
  - Vitamin D deficiency at baseline – defined as Plasma 25-(OH) D concentration of between 15 and 50nmol/L inclusive

### *Exclusion criteria*

1. Inability or unwillingness to comply with the requirements of the study protocol
2. inability or unwillingness to provide written consent
3. Use of Vitamin D supplementation within 3 months of study of screening
4. History of active drug/alcohol dependence or abuse.

For phase 2 of study (intervention)

1. 75g OGTT at baseline confirming established diabetes
2. Vitamin D at screening of > 50 nmol/L or < 15nmol/L
3. History of intolerant or allergy to Vitamin D supplementation
4. Pregnancy
5. Breastfeeding (defined as full breast feeding)
6. Chronic Renal or liver failure, hypercalcaemia, hypocalcaemia or other medical condition (eg. concomitant use of antituberculosis treatment, antiepileptic medications or calcium supplementation) that, in the investigator’s judgement, may be associated with increased risk to the subject or may interfere with study assessments or outcomes.

### *Recruitment and Screening*

Potential participants will be identified and recruited for the study from the following sources:

- Investigator
- Co-investigators
- Physician referrals
- Institutional database

Screening – birth record from Penang General hospital Maternity Unit will be used to identify women with GDM who has delivered 6-24 months prior to study commencement. Suitable women are invited for screening

### *Subject withdrawal & drop-out*

Subjects are free to withdraw from the study at any time for any reason. Subjects may also be withdrawn from the study at any time at the discretion of the investigator.

### *Procedures for handling withdrawal*

Subjects who withdraw or are withdrawn from the study should:

- Have the reason(s) for their withdrawal recorded
- Be asked about the presence of any AEs
- Be seen by an investigator and all final assessments will be performed and recorded
- Have study treatment returned.

# TREATMENT AND STUDY PROCEDURES

## Description of study drug/intervention and comparator

Vitamin D3 capsule in the form of Blackmore’s Vitamin D3 1000iu soft gel capsule will be used. Each softgel capsule will contain 1000iu of Vitamin D3. Patient enrolled in study will take daily- 4 softgel capsules of vitamin D3 or matching placebo.

### *Storage*

Vitamin D3 / Placebo can be kept at room temperature and only accessible to authorised study personnel.

### *Dispensing*

Each patient will be dispensed sufficient medication for 8 weeks of therapy.

Upon dispensation, the investigator will record the following:

- subject ID and initials
- date dispensed,
- total bottles dispensed, batch number and expiry date of product

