## Assessment of compliance

Accountability and subject compliance will be assessed by maintaining adequate "drug dispensing" and return forms. Subjects will be required to return all unused study medication, and the pill count will be entered into the CRF.

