### *8.1.4 .Visit 4*

Visit 4 occur at 8 (+/-1) weeks post randomization -

The investigator will perform the following procedures:

- - Record any change of dose administration of study treatment
  - Record any AE or SAE
  - Dispense study treatment
  - Measure serum calcium, phosphate and albumin level

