### *8.1.5.Visit 5*

Visit 5 occur at 16 (+/-1) weeks post randomization -

The investigator will perform the following procedures:

- - Record any change of dose administration of study treatment
  - Record any AE or SAE
  - Dispense study treatment

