## Sample handling and analysis

## Collection

105 ml of blood will be drawn for through the 6 months study duration- consisting of:

50 ml of blood will be drawn at screening visit (wk -2) for –

UE, creatinine, LF, Calcium and phosphate, fasting lipid profile, HsCRP (5ml)

plasma 25(OH) vit D ( 5ml)

OGTT at time 0, 60,90 and 120 min for glucose ( 20ml) and insulin ( 20ml)

5 ml of blood will be drawn at visit 4 (wk 8) for-

Calcium, phosphate and albumin (5 ml)

50ml of blood will be drawn at study completion ( wk 24) for-

Calcium, phosphate and albumin, fasting lipid profile, HsCRP (5ml)

plasma vit D ( 5ml),

OGTT at time 0, 60,90 and 120 min for glucose (20ml) and insulin ( 20ml)

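### Each dispensing is stated to cover 8 weeks, but the visit windows allow 9 to 10 weeks between visits and the end is both week 24 and 6 months, so women who attend on time can run out of capsules

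*Protocol*

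**What the plan says.** **Supply.** The Dispensing section states: "Each patient will be dispensed sufficient medication for 8 weeks of therapy". It also has the investigator record the dispensing date and the number of bottles. No overage is mentioned, and none is ruled out. The description of the study drug gives the daily intake: "Patient enrolled in study will take daily- 4 softgel capsules of vitamin D3 or matching placebo".

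**Visit windows.** Section 8.1.4 says "Visit 4 occur at 8 (+/-1) weeks post randomization" and the section on Visit 5 says "Visit 5 occur at 16 (+/-1) weeks post randomization". The design section has a general rule: "All subjects will be seen every 8 weeks (+/-1 week) to be dispensed supply of Vitamin D or placebo". Visit 6 has no window.

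**End of treatment.** The synopsis and the rationale for the regimen give a treatment duration of 6 months, and the description of Visit 6 in the design section says "At the end of 6 months- all subjects will attend fasting and have". The schedule table puts Visit 6 at 24 weeks, and the Collection section says "50ml of blood will be drawn at study completion ( wk 24) for".

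**Returns.** The compliance section says: "Subjects will be required to return all unused study medication, and the pill count will be entered into the CRF". It does not say whether capsules come back at each visit or only at the end, or whether counted capsules may be handed back.

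**Analysis set.** Section 10.3.1 describes a single per-protocol analysis, which leaves out women who did not get their treatment as planned.

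**The concern.** The stated supply equals the nominal gap between visits, while the windows permit longer gaps. The protocol therefore does not guarantee capsules for a woman who follows it fully. Two things are at stake.

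- **Evaluable women.** Section 10.3.1 excludes women not treated as planned, so an interruption caused by the plan could remove a compliant woman. Section 10.1 plans 13 per arm and needs 9, a margin of 4 per arm that is already meant to absorb loss to follow-up and unplanned pregnancy.
- **The final measurement.** The last visit yields the primary outcomes (glucose and insulin AUC, HOMA-IR) and the 25(OH)D level used to judge whether the regimen reaches its target. An untreated spell just before that visit would blur both answers.

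**Working it through.** **Inputs.** Visit 3 is week 0. Visit 4 is at week 7, 8 or 9 (section 8.1.4). Visit 5 is at week 15, 16 or 17 (section on Visit 5). The end is week 24 (schedule table, Collection). Each of the three dispensings covers 8 weeks (Dispensing). Assumptions: every capsule is taken, and there is no overage.

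**Nominal schedule.** 3 × 8 = 24 weeks, so dispensing at weeks 0, 8 and 16 reaches week 24 exactly. There is no gap.

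**Longest permitted intervals.**
- Visit 3 to Visit 4: 9 − 0 = 9 weeks.
- Visit 4 to Visit 5: 17 − 7 = 10 weeks, or 9 if the general rule limits each interval to 8 ± 1 weeks.
- Visit 5 to week 24: 24 − 15 = 9 weeks.

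**Gap formulas.**
- Leftovers taken back when new stock is issued: gap = max(0, interval − 8) for each interval.
- Leftovers carried forward: stock = carry-over + 8; gap = max(0, interval − stock); new carry-over = max(0, stock − interval).

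Example, Visit 4 at week 7 and Visit 5 at week 17 (intervals 7, 10, 7): taken back, the gaps are 0, 2 and 0 weeks. Carried forward, 1 week is left at Visit 4, so stock is 9 weeks and the gap is 10 − 9 = 1 week.

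All nine patterns, in weeks, with the end at week 24:

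| Visit 4 | Visit 5 | Intervals | Total gap, taken back | Of which just before OGTT | Total gap, carried forward |
|---|---|---|---|---|---|
| 7 | 15 | 7, 8, 9 | 1 | 1 | 0 |
| 7 | 16 | 7, 9, 8 | 1 | 0 | 0 |
| 7 | 17 | 7, 10, 7 | 2 | 0 | 1 |
| 8 | 15 | 8, 7, 9 | 1 | 1 | 0 |
| 8 | 16 | 8, 8, 8 | 0 | 0 | 0 |
| 8 | 17 | 8, 9, 7 | 1 | 0 | 1 |
| 9 | 15 | 9, 6, 9 | 2 | 1 | 1 |
| 9 | 16 | 9, 7, 8 | 1 | 0 | 1 |
| 9 | 17 | 9, 8, 7 | 1 | 0 | 1 |

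With leftovers taken back, 8 of 9 patterns have a gap, and 3 of 9 (Visit 5 at week 15) have one just before the final OGTT. With leftovers carried forward, 5 of 9 have a 1-week gap, none of them just before the OGTT.

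**Literal 6 months.** 365.25 / 2 = 182.6 days, or 26.1 weeks. Three supplies give 3 × 56 = 168 days. The shortfall is 182.6 − 168 = 14.6 days, about 2.1 weeks. On the nominal dates all of it falls just before the final OGTT. Over the nine patterns, the part just before the OGTT is 1.1 to 3.1 weeks if leftovers are taken back, and 1.1 or 2.1 weeks if they are carried forward.

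**The case against.** Several stronger readings are tempting, and the protocol does not support them.

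- A reader might infer that each woman receives precisely 56 days of capsules. The wording sets a minimum, and bottles are recorded, so overage may occur in practice. It is not required, however.
- A reader might infer that women who keep every rule will run out. With an end at week 24 that is not general: the nominal dates leave no gap, and a visit one day late leaves only a one-day gap. The nine patterns are window limits and nominal dates, not probabilities, so 8 of 9 says nothing about how many women would be affected.
- A reader might infer that early visits never build a reserve. That assumes leftovers are taken back at follow-up visits. Pill counts at those visits make this plausible, but the compliance section does not say so.
- A reader might take the 6-month shortfall as certain. The Collection section describes one timeline as lasting 6 months and ending at week 24, which suggests a rounded label. The literal reading is the weaker one, though the text does not exclude it.
- A reader might infer that pill counts would hide a gap. They need not: no capsules returned 63 days after a 56-day supply was issued reveals it, and the dispensing date is recorded.
- The effect on results is not shown. A gap of 7 to 14 days is 4% to 8% of 168 days, and section 10.3.1 sets no adherence threshold, so exclusion is possible rather than certain.

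What remains is that the protocol states no overage, that its windows exceed the stated supply, and that it gives the end of treatment in two ways.

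**Conclusion.** The point holds as a conditional one. Women attending within the windows can be without capsules for up to 1 to 2 weeks in total when the end is week 24, assuming full intake and no overage. The 2-week figure needs leftovers to be taken back under the windows counted from randomisation; with leftovers carried forward the maximum there is 1 week. A gap just before the week-24 OGTT and 25(OH)D arises only with an early Visit 5 and leftovers taken back. If 6 months is literal, supply falls about 14 days short for every woman. The loss of evaluable women under section 10.3.1 is a risk the plan permits, not a demonstrated loss. This is worth correcting before dispensing starts, since supply, windows and duration are matters for the protocol itself.

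**What to change.** Reconcile the synopsis, the rationale for the regimen, the visit descriptions in the design section and in section 8, the Dispensing and compliance sections, the schedule table and the Collection section, so that:

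- the supply at each dispensing covers the longest interval the stated windows allow, with a statement on whether those windows run from randomisation or from the previous visit;
- the handling of returned capsules is stated and fits that supply;
- one definition of the end of treatment serves both supply and Visit 6.

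The dose and the choice between 24 weeks and 6 months remain with the sponsor. Two neighbouring inconsistencies belong in the same edit: the rationale gives 2 capsules daily while the drug description gives 4, and the schedule table marks dispensing at the final visit.

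The cost is a wording change and spare capsules. For an end at week 24, covering intervals of 9, 10 and 9 weeks adds 1 + 2 + 1 = 4 weeks per woman. At the 4 capsules a day in the drug description that is 4 × 28 = 112 capsules each, or 26 × 112 = 2,912 in all, with the unused ones returned and counted. A literal 6 months would add about 14.6 × 4 ≈ 58 more per woman.

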### *Accountability*

The investigator or designee must maintain current and accurate record of the receipt, inventory and dispensing, including shipping invoices, of all study supplies.

Accountability logs must be available for inspection at any time.

## Concomitant medication/treatment

- Vitamin D intake are not allowed within 3 months of screening period
- Use of any oral hypoglycaemic agents not allowed
- All other concomitant medicines/therapies are recorded and permitted during the study

## Blinding & Unblinding procedures

This is a double blind study- All subjects and assessors will be blinded to the study medication during the trial. Independent central block randomization will be done with help of CRC Hospital Pulau Pinang In the event that an AE or pregnancy occurs for which knowledge of the identity of the test drug is necessary to manage the subject's condition, blinding may be broken and patient identified to be on either Vitamin D or Placebo.

## Assessment of compliance

Accountability and subject compliance will be assessed by maintaining adequate "drug dispensing" and return forms. Subjects will be required to return all unused study medication, and the pill count will be entered into the CRF.

# EFFICACY & SAFETY ASSESSMENTS

## Assessment of efficacy

Efficacy of Vitamin D replacement will be assessed with parameters below:

- Primary criterion
  - Change in glucose metabolism as assessed by area under curve for glucose (AUCgluc) and insulin (AUC ins) post 75 g OGTT
  - Change in Insulin sensitivity index as calculated by HOMA –IR^28^
- Secondary criteria
  - Change in Insulin Sensitivity index as calculated by QUIKI^27^
  - Change in dynamic Insulin Sensitivity using OGTT Insulin Sensitivity (OGIS)^25,26^
  - Change in Beta cell function as evaluated by ratio of AUCins to AUCgluc^29^
  - Change in Blood pressure (BP), Body Mass Index (BMI) and Waist Hip Ratio (WHR)
  - Change in fasting lipid profile, HsCRP and urinary Microalbumin creatinine ration
  - Change in plasma 25-OH- Vitamin D level pre and post replacement

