# 10 STATISTICAL METHODS

## 10.1 Sample size and power considerations

Using AUC insulin:
By using nQuery Advisor version 6.01, from paper written by Gedik et al (Effects of vitamin D deficiency and repletion on insulin and glucagon secretion in man ^)16^, a sample size of 4 will have 95% power to detect a difference in means of -4.610 (e.g. the First condition mean, µ1, of 9.090 and a Second condition mean, µ2, of 13.700), assuming a standard deviation of differences of 1.200, with a 0.050 two-sided significance level. By adding 40% dropped out patient in case of lost to follow up unplanned pregnancy, the total sample for 2 arms (placebo and treatment group) treatments is 11 patients.

Using HOMA-IR:
By using nQuery Advisor version 6.01, from paper written by Von Hurst et al (Vitamin D supplementation reduces insulin resistance in South Asian women living in New Zealand who are insulin resistant and vitamin D deficient - a randomised, placebo-controlled trial )^31^, a sample size of 9 will have 95% power to detect a difference in means of 0.700 (e.g. the differences between Group 1 mean, µ1, of 0.800 and a Group 2 mean, µ2, of 0.100), assuming that the common standard deviation is 0.384, with a 0.050 two-sided significance level. By adding 40% dropped out patient in case of lost to follow up or unplanned pregnnacy, the total sample for 2 arms (placebo and treatment group) treatments is 26 patients (13 patients for each arms).

Since the study will be using both efficacy analysis, higher sample calculated using HOMA-IR was chosen as reference ie 26 subjects required for study.

Green et al (Vitamin D status and its association with parathyroid hormone concentrations in women of child-bearing age living in Jakarta and Kuala Lumpur)^15^ found 60% of population to have 25 (OH) Vit D of < 50nmol/L. Assuming a similar prevalence exist in our population, we thus expect to screen at least 44 women to recruit 26 subjects for the study.

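### Three unranked primary measures have no success rule, and the stated 95% power holds only for HOMA-IR tested alone at two-sided 0.05

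*Protocol*

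**What the plan says.** The Protocol section Assessment of efficacy puts two bullets under its primary criterion. The first is "Change in glucose metabolism as assessed by area under curve for glucose (AUCgluc) and insulin (AUC ins) post 75 g OGTT", which is two measures. The second is "Change in Insulin sensitivity index as calculated by HOMA"-IR. The Synopsis (Criteria for evaluation) has the same list. Neither place ranks the three measures, says whether one or all must succeed, or gives a direction of benefit. The hypothesis and the primary objective refer to glucose metabolism only in general terms.

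Section 10.1 contains two calculations:

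- **AUC insulin:** "sample size of 4 will have 95% power to detect a difference in means of -4.610", with condition means of 9.090 and 13.700, a standard deviation of differences of 1.200 and two-sided 0.050. The total after the drop-out allowance is 11.
- **HOMA-IR:** "a sample size of 9 will have 95% power to detect a difference in means of 0.700", with group means of 0.800 and 0.100, "assuming that the common standard deviation is 0.384, with a 0.050 two-sided significance level". The total after the drop-out allowance is 26, or 13 per arm.

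The two are then combined: "Since the study will be using both efficacy analysis, higher sample calculated using HOMA-IR was chosen as reference". AUC glucose has no calculation and no stated significance level. The Synopsis reports only the HOMA-IR calculation.

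**The concern.** Taking the larger of two sample sizes secures the power of one test at an undivided 0.05. It does not settle what the trial will claim. If any one of several primaries can carry the claim, the chance of a false claim rises above 5% unless alpha is divided, and dividing alpha lowers the power below the stated figure. If all must succeed, alpha needs no division, but the relevant power is the joint power, and that needs planning values for every primary measure.

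There is a second gap. The AUC insulin planning values go up from the first condition to the second, so a rise is what was sized. Yet the protocol describes its OGTT measures as markers of carbohydrate tolerance, insulin resistance and insulin secretion. A higher AUC insulin could be presented as better secretion and a lower one as better sensitivity. With a two-sided test and no stated direction, a significant result either way could be described as an improvement after the data are seen.

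**Working it through.** **Inputs, all from section 10.1.** HOMA-IR: difference 0.700, SD 0.384, two-sided 0.05, 9 per group. AUC insulin: difference 4.610, SD of differences 1.200, two-sided 0.05, n = 4. Drop-out allowance 40%.

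**1. Reproducing the protocol's figures.**

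- HOMA-IR, two-sample t-test: d = 0.700/0.384 = 1.823. With n = 9 per group the noncentrality is 1.823 × √(9/2) = 3.867 on 16 df and the critical t is 2.120, so power is 95.2%. With n = 8 it is 92.3%. The stated 9 reproduces, and 9 × 1.4 = 12.6, i.e. 13 per arm and 26 in total.
- AUC insulin, paired t-test: 4.610/1.200 = 3.842. With n = 4 the noncentrality is 3.842 × √4 = 7.683 on 3 df and power is 99.7%. With n = 3 it is 89.0%. The stated 4 reproduces, and 4 × 1.4 × 2 = 11.2, stated as 11.

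Both figures use the full 0.05.

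**2. False-positive risk if any one win counts.** Under independence it is 1 − 0.95^k.

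- Two measures: 1 − 0.95² = 9.75%.
- Three measures, taking 0.05 for AUC glucose as well (an assumption, since the protocol gives it no level): 1 − 0.95³ = 14.3%.

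The three measures come from the same OGTT and will be correlated. The documents give no correlation, so a range is assumed (simulated equicorrelated two-sided z tests):

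| Assumed pairwise correlation | Any of three |
|---|---|
| 0.3 | 13.6% |
| 0.5 | 12.5% |
| 0.7 | 10.9% |
| 0.9 | 8.4% |

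**3. HOMA-IR power if alpha is split equally (Bonferroni).**

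| Per arm | 0.05 | 0.025 (two measures) | 0.0167 (three measures) |
|---|---|---|---|
| 9 | 95.2% | 90.5% | 86.8% |
| 8 | 92.3% | 85.7% | 80.8% |

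The row for 8 is included because 13 per arm less 40% is 13 × 0.6 = 7.8. To restore 95% power, HOMA-IR needs 11 per group at 0.025 or 12 per group at 0.0167. With the protocol's own 1.4 multiplier that is 15.4 → 16 per arm (32 in total) or 16.8 → 17 per arm (34 in total).

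**4. If all must win.** No alpha split is needed. For the two sized measures, assume that the paired SD of 1.200 is also the SD of change within each arm. AUC insulin power at 9 per arm is then above 99.99%. With the SD doubled to 2.4 it is 96.9%. Under the first assumption, joint power for AUC insulin and HOMA-IR is about 95% whatever their correlation. For all three measures it cannot be computed, because AUC glucose has no assumed difference or SD.

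**The case against.** The strongest reply is that the error inflation is conditional. Nowhere does the protocol say that one win is enough; 0.05 appears only as a sizing input and no hypothesis test is named. Under an all-must-win rule the false-positive risk is at most 5%, and for the two sized measures the larger sample size is then adequate, as step 4 shows. A decision rule and a multiplicity method may also sit in an SAP that is not at hand. All of this stands, and it rules out saying that the trial's false-positive rate is 14.3%, or that taking the larger sample size is wrong under every rule. It also rules out saying that all three measures are sized or tested at 0.05: AUC glucose has neither a size nor a level.

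It does not remove the point. The three unranked primaries, the undivided alpha in the sizing and the total of 26 are fixed in the protocol itself. A later alpha split would make the stated 95% untrue, and a later all-must-win rule over three measures would have unknown power.

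A reader might also infer that the plan contradicts itself because AUC insulin is planned to rise while HOMA-IR is planned to fall. The documents do not support that. The HOMA-IR means carry no sign; the fall is inferred from the cited trial's title ("Vitamin D supplementation reduces insulin resistance in South Asian women living in New Zealand") and its description in the introduction. Moreover, the introduction treats GDM as involving both insulin resistance and impaired beta-cell function, so more secretion together with less resistance fits the rationale. What is missing is only a statement of which AUC insulin direction counts as benefit.

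Finally, choosing HOMA-IR as sole primary is not the only repair, and it demotes the direct post-load glucose measure although the objective concerns glucose metabolism. That is a real cost, and a sponsor may prefer one of the other routes given under the fix.

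**Conclusion.** The point holds in a conditional form. The protocol has three unranked primary measures, no success rule, and a sample size whose 95% power is correct for HOMA-IR alone at two-sided 0.05 with 9 evaluable women per arm.

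- **Any win counts:** the false-positive risk is 9.75% for the two sized measures and 14.3% for all three under independence, or about 11% to 14% for three at assumed correlations of 0.7 to 0.3. The three-measure figures assume that AUC glucose would also be tested at 0.05.
- **Three-way Bonferroni split:** HOMA-IR power is about 87% with 9 per arm and 81% with 8.
- **All three must win:** error is controlled, but joint power is unknown.

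The missing direction of benefit for AUC insulin is a gap in definition, not an inconsistency. The matter should be settled before unblinding, because as written the primary claim is not defined.

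**What to change.** In the Synopsis and in Assessment of efficacy, name change in HOMA-IR as the single primary endpoint, tested at two-sided 0.05. It is the measure that set the total of 26 and the only one whose calculation the Synopsis carries, so the stated power then needs no change on this account. Move AUC glucose and AUC insulin to the secondary criteria. State which direction of AUC insulin counts as benefit, or state that it is read together with OGIS, which is already a secondary measure. Adjust the sentence in section 10.1 that refers to using both analyses.

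The cost is protocol wording, with no new data. The downside is that the AUC results can no longer carry the primary claim on their own.

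If the sponsor keeps all three as primary, the protocol should state the win rule with a matching multiplicity procedure and restate the power:

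- **Any-win rule:** split alpha and re-size. For 95% power HOMA-IR alone needs 12 per group under an equal three-way split, before drop-out.
- **All-must-win rule:** keep 0.05 for each measure, but supply planning values for AUC glucose so that joint power can be given.

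Either way, give AUC insulin a stated direction of benefit.
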